### Statistical analysis

Retrieved data from each patient in both groups will be recorded at baseline and at each follow-up assessment period using Excel, which will then be entered into a software for analysis after the final assessment point has been met. All statistical analysis will be conducted by a third-party (not involved with our research in any way) using the Statistical Analysis System (SAS) Software for Windows (version 9.4, *SAS institute, USA*).

Baseline demographic and clinical variables will be presented in the form of number and percentages for categorical variables, while continuous variables will be presented as means and standard deviations (SD) or median and range if the data were normal or skewed, respectively.

Our primary outcome will be analyzed with the intention-to-treat (ITT) analysis and reported as the mean difference (MD) and corresponding 95% confidence interval (CI) in cartilage-WORMS score between the intervention and control groups using Student’s t-test. Secondary outcomes will then be analyzed at the final assessment. Pain will be analyzed as a categorical outcome using the chi-square test, while the differences in continuous determinants of pain (baseline variables) will analyzed using MANOVA test. The QoL will be analyzed and reported as the mean difference and its corresponding 95% CI between both interventions using t-test. Bone density and osteoporosis severity (measured by the Kellgren-Lawrence scale) will be analyzed as categorical outcomes (normal, low density, osteoporosis) using the Chi-square test. Meanwhile, differences in serum levels of inflammatory biomarkers between both groups will be measured using t-test. In order to account for missing data, survival analyses will be conducted while implementing the “last-observation carried forward” approach. Such data will be presented in Kaplan–Meier curves, showing the numbers of patients analyzed at each assessment timepoint. A *p*-value of less than 0.05 will indicate statistical significance.

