## Background

Osteoarthritis (OA) is a major cause of pain, functional limitations, and disability worldwide [1]. The hip and knee joints are the most common sites of OA-associated disability worldwide [2]. The causes of pain and mechanical dysfunction in osteoarthritis (OA) remain unclear, and previous research have suggested multifactorial causes [3–6]. Injury to one component of the joint leads to a cascade of injuries that lead to further joint dysfunction and clinical manifestations of OA. Currently, only a few features, such as joint space narrowing and osteophytes can be detected on standard radiographs, and determining the severity of disease is limited. Therefore, a broader imaging assessment scale is needed to correctly evaluate joint structural integrity and its role in the symptomatic manifestations of OA.

The Whole-Organ Magnetic Resonance Imaging Score (WORMS) is a good semi-quantitative tool for the study of knee osteoarthritis (KOA). The WORMS score includes cartilage signal and morphology, subchondral bone marrow abnormalities, subchondral cysts, subchondral bone wear, marginal osteophytes, and other features which can comprehensively analyze the morphology and structure of knee OA. The WORMS scoring system requires magnetic resonance imaging (MRI), which not only has no ionizing radiation, but also avoids the morphological aberration, amplification, and superposition seen with computer tomography. More importantly, MRI is well suited for evaluating joint tissues such as cartilage, meniscus, and ligaments, giving it great potential as an imaging tool for the entire joint. The knee MRI scans will be taken using a 1.5-T whole-body MRI unit with a transmit-receive coil. The same scanning unit will be used for all participants in the study center. The sequence and parameters of the used MRI unit is provided in (Supplementary Table 1).

For osteoarthritis (OA), current treatments focus on symptomatic relief, but many patients do not achieve adequate pain control [7]. In addition, despite the high prevalence of OA, there are currently no approved disease-modifying drugs (DMOADs) for OA that would help prevent the joint damage seen along the course of the disease. Therefore, the development of a novel and effective treatment is necessary.

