## Methods/design

### Study design and setting

This is a multicenter, randomized, double-blinded, placebo-controlled study. Upon obtaining Institutional Review Board (IRB)- Ethics Committee’s approval (from each corresponding included center), recruitment of patients will begin. The study is scheduled to start on May 1, 2021, with a completion date on December 31, 2022. Patients will undergo a 1:1 double-blinded randomization to receive a one-year course of alendronate sodium vitamin D_3_ tablets (Gubangjia, The CSPC Ouyi Pharmaceutical Co., Ltd. Shijiazhuang, China) or placebo. The use of Tylenol for pain control will be permitted during the trial; however, it will be monitored and reported for future analysis. In addition, Vitamin D and calcium supplementation will be allowed for usage by study participants. The use of unmarketed drugs or other investigational drugs will be prohibited during the study period; otherwise, such patients will be excluded. Other bisphosphonates (such as zoledronic acid, risedronic acid, etc.) will be prohibited during the study period. Non-steroidal anti-inflammatory drugs and other topical drugs with analgesic effects will be prohibited during the study period. This study will be carried out in three domestic hospitals (Peking Union Medical College Hospital, Zhongshan Hospital of Fudan University, and The Third Affiliated Hospital of Southern Medical University) with a follow-up period of 2 years.

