### Eligibility criteria

#### Inclusion criteria

Patients will be eligible for inclusion if they are consistent will all of the following criteria: (1) adult patients (50–75 years of age) with significant knee pain (defined as pain score ≥ 40 mm on the 100mmVAS scale), (2) having a diagnosis of knee osteoarthritis per the diagnostic criteria of the American College of Rheumatology (ACR) and the Chinese Orthopedic Association, and (3) having a radiographic Kellgren-Lawrence grade I or II knee OA and MRI findings of bone marrow edema-like lesions. The inclusion of bone marrow edema-like lesions (identified by high bone turnover through MRI) is because they are associated with greater response to bisphosphonates [19].

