### Randomization and blinding

Randomization will be performed using a variable-sized block (sizes of 4, 8, and 12), computer-generated randomization procedure to ensure equal number of participants within each treatment arm. The execution of block randomization will be done by the SAS software, where a different block will be implemented each time the value within the parenthesis of the ranuni function of the macro set reaches zero. The assignments will be blinded to both the investigators and study participants and concealed within sealed, fully opaque envelops. Of note, emergency unblinding will only be allowed in critical situations where the safety of included participants is affected.

Allocation concealment will be ensured with the use of sequentially numbered, opaque, sealed envelopes within containers. There will be a coordinating center for this particular step and a particular study personnel will carry out the allocation of patients.

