### Outcome measures

#### Primary outcome

Our primary outcome is to determine the improvement in knee structure following each intervention using an MRI-based scale named the Whole-Organ Magnetic Resonance Imaging Score (WORMS) scale at 6 and 12 months after treatment allocation [20]. The WORMS scale is designed to determine the status of the knee joint in patients with OA in respect to fourteen independent articular features. Five out of the 14 features are related to the articular surfaces, and they include: (1) cartilage signal and morphology, (2) subarticular bone marrow abnormality, (3) subarticular cysts, (4) subarticular bone attrition, and (5) marginal osteophytes. In addition, all of these features are further evaluated in 15 different regions divided by anatomical landmarks in a fully-extended knee (Supplementary Fig. 1). For the purposes of our research, we will focus on cartilage signal and morphology. This feature is scored based on only 14 articular surface regions (excluding region S), with a score ranging from 0 to 6 on an 8-point scale (Supplementary Fig. 2). The WORMS scoring system for cartilage includes 0 = normal cartilage thickness and signal, 1 = normal cartilage thickness but with increased signal, 2 = a partial-thickness defect of < 1 cm in the greatest width, 2.5 = a full-thickness focal defect of < 1 cm in the greatest width, 3 = multiple regions having partial-thickness defects alternating with regions of normal thickness or defects > 1 cm, 4 = diffuse partial-thickness defects, 5 = multiple regions of full-thickness defects or defects > 1 cm, and 6 = diffuse full-thickness defects, with an overall score ranging from 0 to 84.

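### The primary cartilage-WORMS comparison is fixed as an unadjusted t-test, which gives up precision that baseline adjustment would supply at no cost in data

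*Protocol article*

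**What the plan says.** The Statistical analysis section of the protocol article names the primary method: an intention-to-treat comparison, "reported as the mean difference (MD) and corresponding 95% confidence interval (CI) in cartilage-WORMS score between the intervention and control groups", by Student's t-test. No adjusted or mixed model of the primary outcome appears anywhere in the article. The method is therefore stated, not deferred.

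Three statements imply that a baseline cartilage reading will exist:

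- The same section says: "Retrieved data from each patient in both groups will be recorded at baseline and at each follow-up assessment period".
- The inclusion criteria require "having a radiographic Kellgren-Lawrence grade I or II knee OA and MRI findings of bone marrow edema-like lesions", so an MRI is needed at entry.
- The primary outcome is worded as a change: "Our primary outcome is to determine the improvement in knee structure following each intervention".

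On centre, Study design and setting says: "This study will be carried out in three domestic hospitals". Randomization and blinding says: "Randomization will be performed using a variable-sized block (sizes of 4, 8, and 12), computer-generated randomization procedure". It does not mention centre.

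For secondary outcomes, quality of life is also compared by t-test, and "differences in serum levels of inflammatory biomarkers between both groups will be measured using t-test".

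**The concern.** The cartilage feature is scored over 14 regions at 0 to 6 each, for a total of 0 to 84. Knees that enter with different scores will probably still differ a year later, whatever the treatment does. A t-test on the follow-up score counts that pre-existing variation as noise, although it can be explained from the entry reading. A t-test on change removes part of it, but in general not in the most efficient proportion.

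Two things are at stake: the width of the confidence interval for the trial's main question, and the exposure of the estimate to whatever baseline imbalance randomisation happens to leave.

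**Working it through.** **The plan's own figure.** The Sample size calculation section gives 30 per group for 80% power at alpha 0.05 (taken as two-sided) to detect a 2.2% difference at 12 months. No SD is given, so the figure can only be solved backwards:

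- standardised difference = (1.960 + 0.842) × √(2/30) = 0.72
- implied SD = 2.2 / 0.723 = 3.04 percentage points

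The section does not say whether this SD belongs to a score or to a change.

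**Inputs for the comparison.** Allocation is 1:1, with 110 per group after the stated increase. The correlation r between baseline and 12-month score is not in the documents; I assume 0.5, 0.7 and 0.9. I also assume equal SD σ at both times and a linear relation.

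**Variance of the treatment difference, n per group:**

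- t-test on follow-up score: 2σ²/n
- t-test on change: 2σ² × 2(1 − r)/n
- ANCOVA on baseline: 2σ² × (1 − r²)/n (large-sample)

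The ratio of ANCOVA to the follow-up-score test is 1 − r². The ratio to the change-score test is (1 − r²) / [2(1 − r)] = (1 + r)/2. CI width scales with the square root of the ratio.

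| | r = 0.5 | r = 0.7 | r = 0.9 |
|---|---|---|---|
| **Against follow-up score:** variance ratio | 0.75 | 0.51 | 0.19 |
| CI width ratio | 0.87 | 0.71 | 0.44 |
| 110 per group is worth | 147 | 216 | 579 |
| Power at 30 per group, from 80% | 90% | 97.5% | >99% |
| **Against change score:** variance ratio | 0.75 | 0.85 | 0.95 |
| CI width ratio | 0.87 | 0.92 | 0.97 |
| 110 per group is worth | 147 | 129 | 116 |
| Power at 30 per group, from 80% | 90% | 86% | 82% |

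The two readings agree at r = 0.5 and diverge as r rises. The better baseline predicts follow-up, the more adjustment gains over the follow-up score and the less it gains over change.

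**Chance imbalance.** At 110 per group the baseline difference between arms has standard error √(2/110) = 0.135 SD. An imbalance of at least 0.2 SD then occurs in about 14% of such trials. The follow-up-score test carries r times the imbalance into the estimate: 0.7 × 0.2 = 0.14 SD at r = 0.7. The change-score test carries (1 − r) times it in the opposite direction: 0.3 × 0.2 = 0.06 SD. ANCOVA removes the part linearly related to baseline.

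**Score or change under ANCOVA.** Write Y for follow-up, X for baseline and T for treatment. If Y = a + bT + cX, then Y − X = a + bT + (c − 1)X. The coefficient b is the same, so adjustment gives the same treatment estimate on either reading.

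**Centre.** If centre explained an assumed 0 to 10% of the variance, including it would cut variance by a further 0 to 10%, which narrows the CI by at most about 5% (√0.90 = 0.95).

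**The case against.** The strongest reply is that the t-test is valid under randomisation, so this is only a matter of efficiency, and the trial may have efficiency to spare. On the plan's own implied effect of 0.72 SD, 110 per group less 10% loss in the first year leaves 99, and unadjusted power already exceeds 99%. The first part stands. The second rests on an SD that the article never states, so it gives limited reassurance. Estimation is also an aim of the primary analysis, and the interval is wider than it need be at any sample size.

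Several stronger readings are tempting and are not supported:

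- **That the follow-up score is definitely what is tested, so that the trial discards the equivalent of two to five times its size.** The Abstract and the Statistical analysis section speak of the WORMS score. The Trial objectives, the Primary outcome and the Sample size calculation speak of improvement or loss. On the change reading with r of 0.7 to 0.9, the variance falls by only 15% to 5%.
- **That each hospital scans on its own unit and so adds a scanner effect.** The Background says only: "The same scanning unit will be used for all participants in the study center". The number of units is not given.
- **That allocation is not stratified by centre.** The article is silent, and a condensed article may omit stratification factors.
- **That the biomarker t-tests lose a known amount of power through skewness.** The article gives no distribution, SD or expected effect for any biomarker.

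It is also fair to say that a baseline WORMS reading is implied and not listed in so many words.

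**Conclusion.** The point holds as one of precision. The article fixes an unadjusted t-test for its primary outcome when baseline adjustment is very probably available. Adjustment does not increase the large-sample variance.

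For r between 0.5 and 0.9, the CI would be 13% to 56% narrower than with a follow-up-score t-test, or 3% to 13% narrower than with a change-score t-test. The size depends on r, on roughly equal SDs at the two times, and on which form of the outcome is meant; the article settles none of these. If change is meant and r is high, the gain is small. Centre is a secondary and modest matter. The t-test result would not be biased, and the plan is not invalidated. This is a change worth making, not a condition for the trial to proceed.

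**What to change.** Before unblinding, prespecify as primary an ANCOVA of 12-month cartilage-WORMS, or the 12-month contrast of a repeated-measures model over 6 and 12 months, with treatment, baseline cartilage-WORMS and centre as terms. Report the adjusted mean difference with its 95% CI, and keep the t-test as supportive. The ANCOVA gives the same treatment estimate whether score or change is the outcome, so it also removes the ambiguity between the two. State explicitly that the entry MRI is scored for cartilage.

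Use the same baseline adjustment for SF-36 and the inflammatory biomarkers where baseline values are collected; the Secondary outcomes section lists them at 3, 6 and 12 months only.

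The cost is analysis wording, with no new patients or visits, provided that the entry scan is scored as the baseline-recording statement implies.

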#### Secondary outcomes

We have seven pre-identified secondary outcomes: WORMS score (at 24 months), pain intensity (at 2, 4, 8, and 12 weeks after enrollment), quality of life (QOL), bone density, risk of knee replacement, severity of knee OA, and estimation of inflammatory biomarkers.The structure of knee joint will be measured using the WORMS scale at 24 months after treatment.Knee pain will be measured in both groups at 2, 4, 8, and 12 weeks after enrollment using the 100-mm visual analogue scale (VAS), which has already been shown to be valid and reliable in measuring pain [21]. Overall ratings range from 0 to 100 mm, where 0–4 mm indicate no pain, 5–44 mm indicate mild pain, 45–74 mm indicate moderate pain, and 75–100 mm indicate severe pain.Quality of life in both groups will be assessed at 3, 6, and 12 months after enrollment using the previously validated Chinese version of the SF-36 questionnaire [22], which is used to measure health status based on eight categories: (1) physical activity, (2) social activity, (3) physical role, (4) energy and emotional status, (5) mental health, (6) vitality, (7) body pain, and (8) general health. The overall score ranges from 0–100, with higher scores reflecting better health-related QoL [23]. This version of the SF-36 questionnaire shows comparable validity and reliability to the original version.Bone density of the lumbar spine and the hip and knee joints will be carried out using dual-energy x-ray absorptiometry (DXA) at 12 and 24 months after enrollment. Bone density data will be obtained using a Prodigy DXA scanner (GE Healthcare, Madison, USA) and the obtained data will be analyzed according to the manufacturer’s software. The lumbar spine (L1-L4) and the hip (particularly the femur neck and total hip) will be scanned in the supine position using posteroanterior projections.The risk of knee replacement will be evaluated based on a set of baseline and clinical variables and then incorporated into a multivariable logistic regression model to identify significant predictors of knee replacement in patients with OA.Severity of OA will be measured at 12 and 24 months after enrollment using the Kellgren-Lawrence grading scale [24]. The scores of this grading scale range 0 to 4, where 0 indicates no features of OA, 1 indicates questionable osteophytes, 2 indicates definite osteophytes without narrowing in the joint space, 3 indicates definite osteophytes with moderate narrowing, and 4 indicates definite osteophytes with severe narrowing.The serum level of the following inflammatory biomarkers will be measured at 3, 6, and 12 months after enrollment: interleukin (IL)-6, tumor necrotic factor (TNF)-alpha, erythrocyte sedimentation rate (ESR), and C-reactive protein (CRP).

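### Pain, SF-36 and biomarkers are measured at three or four visits but compared by single unadjusted tests at an undefined final assessment, with no stated use of the earlier visits

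*Protocol article*

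**What the plan says.** The Secondary outcomes section sets repeated schedules:

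- Pain: "Knee pain will be measured in both groups at 2, 4, 8, and 12 weeks after enrollment".
- SF-36: "Quality of life in both groups will be assessed at 3, 6, and 12 months after enrollment".
- Blood markers (IL-6, TNF-alpha, ESR, CRP): "inflammatory biomarkers will be measured at 3, 6, and 12 months after enrollment".

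The Statistical analysis section then states "Secondary outcomes will then be analyzed at the final assessment" and gives each outcome a two-group test:

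- "Pain will be analyzed as a categorical outcome using the chi-square test".
- "The QoL will be analyzed and reported as the mean difference and its corresponding 95% CI between both interventions using t-test".
- For the markers, "differences in serum levels of inflammatory biomarkers between both groups will be measured using t-test".

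None of these sentences names a visit, a baseline covariate or a model across visits. The MANOVA mentioned beside the pain test concerns baseline variables, so it adds no comparison of arms at follow-up visits. The missing-data provision is "last-observation carried forward", placed in a sentence about survival analyses and Kaplan–Meier display. Study design and setting gives two years of follow-up.

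**The concern.** The analysis rule does not match the outcome definitions. Patients complete questionnaires and give blood at visits for which no comparison between arms is stated. The rule also relies on a visit that the text does not define for these outcomes, so an analyst could not tell from it which measurement to test.

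Patients who leave before the last visit are the practical problem. If carry-forward is applied to SF-36 or the markers, a month-3 or month-6 value is treated as if it had been observed at month 12. If it is not applied, those patients drop out of the last-visit test even though they gave usable earlier data. Neither is a good basis for the secondary hypothesis on pain, quality of life and biomarkers in the Trial objectives section.

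**Working it through.** The plan gives no figure of its own on this point, so there is none to reproduce. The check has four steps.

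**1. Schedule against analysis**

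| Outcome | Scheduled follow-up visits | Stated test | Scheduled at 24 months? |
|---|---|---|---|
| Pain (VAS) | 4 (weeks 2, 4, 8, 12) | chi-square, no visit named | no |
| SF-36 | 3 (months 3, 6, 12) | t-test, no visit named | no |
| Four biomarkers | 3 (months 3, 6, 12) | t-test, no visit named | no |

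If each outcome is tested at its own last visit, the share of visits without a stated comparison is (k − 1)/k: 3/4 = 75% for pain, and 2/3 = 67% each for SF-36 and biomarkers. In total that is 3 + 2 + 2 = 7 of 4 + 3 + 3 = 10 outcome-visits. Counting the four markers separately gives 3 + 2 + 8 = 13 of 4 + 3 + 12 = 19, or 68%.

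**2. What the final assessment could mean**

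- Each outcome's own last visit: the 7 of 10 above have no stated comparison.
- The trial's last visit at 24 months: 0 of 10 outcome-visits fall there, so there is nothing to test.
- Only the moment at which the analysis is run: the comparison visit is then unnamed for outcomes measured three or four times.

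Each reading leaves something to repair.

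**3. Early leavers**

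The Sample size calculation section expects about 10% lost per year and a total of 220. By month 12 that is 0.10 × 220 = 22 patients without a month-12 SF-36 or biomarker value. The text does not settle whether those values are carried forward or left out.

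**4. Precision**

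The document gives no within-patient correlation. I assume an equal correlation r of 0.5, 0.6 or 0.7 between any two measurements, baseline included, and a continuous outcome.

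| Variance ratio | r = 0.5 | r = 0.6 | r = 0.7 |
|---|---|---|---|
| Mean of 3 visits / last visit, unadjusted: (1 + 2r)/3 | 0.67 | 0.73 | 0.80 |
| Mean of 3 visits / last visit, both baseline-adjusted: [(1 + 2r)/3 − r²]/(1 − r²) | 0.56 | 0.58 | 0.61 |
| Last visit adjusted / last visit unadjusted: 1 − r² | 0.75 | 0.64 | 0.51 |

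The first two rows are reductions of 20-33% and 39-44%, and they concern the average-over-visits effect. The third row concerns the last-visit contrast itself. That gain comes from the baseline value and needs no intermediate visits.

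**The case against.** The strongest reply is that the text nowhere says the earlier visits are excluded. A reader might infer that they never enter a comparison, but that goes beyond the wording. The sentence may describe when the analysis is run, since the same section uses similar words for the start of data entry into the software. The abstract refers to secondary endpoints at several time points, and the Kaplan–Meier sentence refers to numbers analysed per time point. This stands as far as certainty goes. It does not remove the problem: the timing reading repeats what the section has already said and still leaves the comparison visit unnamed.

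Choosing one visit per secondary outcome is also legitimate, and it limits multiple testing. Ten independent tests at 0.05 would give 1 − 0.95^10 = 0.40 as an upper illustration, since visits are correlated. This stands, and the fix keeps a single headline visit.

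A reader might also infer that the plan loses 20-44% in precision on each of these outcomes. The documents do not support that. The figures belong to a different estimand, and averaging in early visits could dilute an effect that builds up over a one-year course. With complete data, a mixed model with arm-by-visit terms and unstructured covariance gives essentially the same last-visit contrast as a last-visit analysis with the same covariates. Nor do the figures apply to pain as planned, which has four visits and is analysed in categories.

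Nor can one say that 22 patients will have carried-forward values, because the text ties that rule to survival analyses. Finally, model details may sit in an analysis plan that is not shown. That is fair for covariance structure and the like, but the article does fix an analysis rule here, and that rule does not fit its own schedules.

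**Conclusion.** The point holds as an inconsistency with a better alternative at hand. Pain, SF-36 and biomarkers are defined at several visits, yet the plan states single unadjusted tests at a final assessment that is undefined for outcomes ending at week 12 or month 12 in a 24-month trial. On the plain reading, 7 of 10 outcome-visits have no stated comparison, and early leavers (about 22 of 220 by month 12, on the plan's own loss figure) are handled either poorly or not at all.

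For the named-visit contrast, the gain comes from baseline adjustment (variance 25-49% lower under the assumed r of 0.5-0.7) and from using dropouts' observed visits, which is likely to be modest at 10% loss. These are secondary outcomes, so the point does not threaten the primary conclusion. It should be corrected before unblinding.

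**What to change.** Name the comparison visit: week 12 for pain, month 12 for SF-36 and for each biomarker. For each outcome, fit one linear mixed model for repeated measures to all scheduled visits, with arm, visit, arm-by-visit, the baseline value and centre. Take the named-visit contrast as the headline estimate with its 95% CI, and report the average over visits as supportive. Do not carry values forward. The model uses patients' observed visits under a missing-at-random assumption, which should be stated.

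The cost is revised wording and slightly more programming, with no new patients, visits or data. The main downside is that VAS pain must be analysed as continuous; the pain categories can still be tabulated descriptively.

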### Sample size calculation

Based on a previous observation, the mean annual loss of the medial tibial cartilage volumes in knee OA patients is 4.5% [25]. The monthly intake of vitamin D (50,000 IU) would result in a serum vitamin D3 level > 60 nmol/L [26], and this, in turn, has been reported to correlate with a 2.2% annual absolute reduction in cartilage loss [27]. This can be translated into a risk reduction of 22% for knee replacement over a period of 2 years [28]. Our sample size calculation was conducted based on Cohen’s formula [29]. With a power level of 80% and alpha level of 0.05, 60 participants (30 in each group) were required to detect a 2.2% between-group difference in terms of medial tibial cartilage loss (WORMS scale) during the second assessment time-point (12 months). Losses to follow-up were not considered in our initial sample size calculation (*NCT04739592*); however, given the fact that both interventions will be administered for a year and patients will be followed up for 2 years after enrollment, we anticipate that around 10% will be lost to follow-up each year, so we increased our final sample size to 220 participants (110 in each group).

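### Knee pain is collected as a continuous VAS but tested as categories by chi-square, and the VAS stops at week 12 of a one-year treatment

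*Protocol article*

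**What the plan says.** Under Secondary outcomes: "Knee pain will be measured in both groups at 2, 4, 8, and 12 weeks after enrollment", on a 0–100 mm scale. The same section gives a key of four bands: none (0–4 mm), mild (5–44), moderate (45–74) and severe (75–100). No later VAS is listed.

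Under Statistical analysis: "Secondary outcomes will then be analyzed at the final assessment", and for pain: "Pain will be analyzed as a categorical outcome using the chi-square test". That section does not name the categories or the week. Quality of life and the biomarkers, also continuous, are compared by t-test, and quality of life is to be reported as a mean difference with 95% CI.

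Study design and setting gives one year of treatment and two years of follow-up. WORMS is read at 6, 12 and 24 months. The SF-36, which has a body pain domain, is taken at 3, 6 and 12 months. Trial objectives names pain in the main aim and in the secondary hypothesis, without a time point.

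**The concern.** Two choices limit what the trial can say about pain.

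1. **The test.** An unordered chi-square on bands uses neither the order of the bands nor the distance between values within one. It takes no account of baseline pain. If only the last VAS is used, weeks 2, 4 and 8 drop out. The reader gets a p-value and no treatment difference in mm.

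2. **The schedule.** The VAS covers 12 of 52 treatment weeks (23%). At 6, 12 and 24 months, when structure is read, there is no knee-pain VAS to set beside it. The trial therefore cannot show on its own pain instrument whether an early effect lasts to the end of treatment.

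The rule on when secondary outcomes are analysed adds a conflict. If it means each outcome's last measurement, pain is analysed at week 12. If it means the last visit at 24 months, there is no VAS to analyse.

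**Working it through.** **The plan's own figure.** There is none for pain. The stated sample size is for cartilage: "With a power level of 80% and alpha level of 0.05, 60 participants (30 in each group) were required", for a "2.2% between-group difference in terms of medial tibial cartilage loss (WORMS scale"), with no SD printed, so the 60 cannot be checked. The dropout step does not reproduce either. The article gives its assumption as "we anticipate that around 10% will be lost to follow-up each year" and arrives at 220 (110 per arm), but 60 / (1 − 0.20) = 75. That is a separate matter. I take 110 per arm as the stated size and also show smaller arms.

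**Inputs.**
- From the document: four bands; 110 per arm; alpha 0.05 (two-sided assumed); about 10% loss per year. At week 12 that leaves 110 × (1 − 0.10 × 12/52) ≈ 107 per arm.
- Assumed, because the document gives none: normal VAS at follow-up, SD 15–25 mm, control mean 30–60 mm, baseline correlation 0.5 for ANCOVA.

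**Formulas.**
- t-test: noncentrality (squared scale) λ_t = n(δ/SD)²/2.
- Four-band chi-square: λ_c = n Σ (p1k − p2k)² / (p1k + p2k). Power is the probability that a noncentral chi-square with 3 df exceeds 7.815.

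**One case in full** (n = 110, SD 20, control mean 50). A t-test has 80% power at δ = 0.3795 × 20 = 7.6 mm, with λ_t = 110 × 0.3795²/2 = 7.92. Cutting at 4.5, 44.5 and 74.5 mm gives these band probabilities:

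| Band (mm) | Control | Active |
|---|---|---|
| 0–4 | 0.0115 | 0.0290 |
| 5–44 | 0.3802 | 0.5126 |
| 45–74 | 0.4981 | 0.4041 |
| 75–100 | 0.1103 | 0.0543 |

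λ_c = 110 × (0.0076 + 0.0196 + 0.0098 + 0.0191) ≈ 6.17, so power is 0.53 and the relative loss is 1 − 0.53/0.80 = 34%. The chi-square keeps 6.17/7.92 = 78% of the signal. The rest of the gap is the cost of 3 df instead of 1.

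**Whole grid, difference set so that the t-test has 80% power:**

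| Per arm | Chi-square power | Relative loss |
|---|---|---|
| 110 | 0.41–0.56 | about 30–50% |
| 89 | 0.40–0.56 | about 30–50% |
| 24–30 | 0.38–0.54 | 33–53% |

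**Fixed differences**, simulated with 107 per arm, follow-up mean 45, SD 22, baseline N(60, 14) truncated to 40–100, values clipped to 0–100:

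| Difference | Chi-square | t-test | ANCOVA | Loss vs t-test | Loss vs ANCOVA |
|---|---|---|---|---|---|
| 8 mm | 0.48 | 0.75 | 0.85 | 36% | 44% |
| 10 mm | 0.70 | 0.91 | 0.96 | 23% | 27% |
| 12 mm | 0.86 | 0.97 | 1.00 | 11% | 14% |

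Changing the SD at 110 per arm and 10 mm gives a loss against the t-test of 17–19% (SD 20) and 25–29% (SD 25). With no true difference, the chi-square rejected in 4.1% of simulated trials (88 per arm), so its error rate is under control.

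**Schedule.** VAS at weeks 2, 4, 8 and 12, set against WORMS at months 6, 12 and 24: no shared time point. SF-36 at months 3, 6 and 12: shared with WORMS at 6 and 12, not at 24.

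**The case against.** The best defence is that the article is a condensed account. It gives the bands as a key for reading the scale, and the exact categories and time point may be set out elsewhere. Pain is a secondary outcome with no stated power, and the test is valid. This stands in part: the four bands and week 12 are inferred. It does not answer the main point, because categorising pain, using chi-square and ending the VAS at week 12 are all stated choices.

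A reader might infer more than the document supports:

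- **A fixed loss of a third or more of the power.** The size depends on assumed inputs and shrinks to about 10% for a large difference.
- **Most of the information is wasted.** In the worked case 78% of the signal is kept.
- **No pain data at all after week 12.** The SF-36 body pain domain runs to 12 months. It belongs to the quality-of-life outcome and is not knee-specific, but it exists.
- **The bands clash with the entry rule** ("defined as pain score ≥ 40 mm on the 100mmVAS scale"), so that a patient entering at 40–44 mm and improving within the mild band counts as unchanged. The chi-square compares the arms at follow-up, and nothing in the plan scores change between bands.
- **The MANOVA is a faulty treatment comparison.** The plan applies it to baseline variables and does not offer it as one.

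**Conclusion.** The point holds as an avoidable inefficiency and a gap in the schedule. It is not a source of bias. Against a t-test on the same data, the categorical analysis loses about 30–50% of power in relative terms where the t-test would have 80%, and about 10–30% for true differences of 10–12 mm with 107–110 per arm (SD 20–25 mm). These figures rest on the four-band, week-12 reading and on a VAS mean, SD and effect that the document does not give. Two findings need no assumption: the stated pain test yields no estimate in mm, and no knee-pain VAS is listed at 6, 12 or 24 months. The time point of the pain analysis also needs to be stated, since one of its two readings leaves nothing to analyse. Because pain is secondary, this should be changed but does not threaten the primary analysis.

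**What to change.** 1. Analyse the VAS in mm with a model adjusted for baseline VAS: ANCOVA at the named time point, or a repeated-measures model over all visits. Report the mean difference with its 95% CI.
2. Keep the four bands as a descriptive table only.
3. Add the one-item VAS at the existing 6-, 12- and 24-month assessments.
4. State which time point is meant by the final assessment for pain.

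Items 1, 2 and 4 are changes of wording. Item 1 needs no new baseline measurement, since a VAS score is already required for eligibility. Item 3 adds one question at three assessments already planned, so the cost is a slightly longer case report form. If item 3 is not adopted, the article should say that its VAS results concern the first 12 weeks only.
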